### Identification of participants and eligibility

#### Inclusion criteria

HCWs: Any frontline adult (aged 18+ years) HCW who provides services for a client living with dementia who is receiving home care services funded by the government Home Care Packages Program or Commonwealth Home Support Programme.

Clients: Adult with a diagnosis of dementia (of any type and stage) or screen positive on the Noticeable Problems Checklist [16] and receiving home care services funded by the Australian Government Home Care Packages Program or Commonwealth Home Support Programme. The Noticeable Problems Checklist is used instead of a formal cognitive screen to minimise client distress and so service providers can refer potentially eligible participants.

Family carers: Adult who cares for a participating client in this study. The family carer must know the client well and spend a minimum of 6 h with the client each week.

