### Outcome measures

Measures are obtained at three time-points (periods 1, 2, and 3: baseline, 6 months, and 12 months respectively). See Fig. 2 for the timing of outcome assessments.

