### Secondary outcomes

HCWs will be assessed on their general knowledge of dementia using the Dementia Knowledge Assessment Scale (DKAS) [22]. Their attitudes towards people living with dementia will be assessed using the Dementia Attitudes Scale (DAS) [23], though the scale has been modified to change the term ‘ADRD’ (Alzheimer’s disease and related disorders) to ‘dementia’ for consistency with the other measures used. The stress experienced by HCWs in providing dementia care will be assessed using the Strain in Dementia Care Scale (SDCS) [24].

For clients living with dementia, their sense of control over daily personal life and social activities will be assessed by HCWs or family carers, using the Adult Social Care Outcomes Toolkit ASCOT-SCT4 [25]. Information about client experiences when receiving home care will be assessed using the Consumer Experience Report Pilot Draft (CER-Draft, new scale) [26]. The health-related quality of life of clients will be assessed using the Dementia Quality of Life (DEMQOL) [27] or proxy version (DEMQOL-Proxy). Family carers rate the presence and severity of client neuropsychiatric symptoms, as well as the level of caregiver distress resulting from the symptoms, using the Neuropsychiatric Inventory (NPI-12) [28]. Functional daily activities of people with dementia in community dwelling will be assessed using the Disability Assessment for Dementia Scale (DAD) [29]. Caregiver personal and role strain will be assessed by the family carer using the Zarit Burden Interview (ZBI) self-report scale [30].

By improving staff dementia knowledge, attitudes, confidence, and competence, it will likely improve the overall quality of dementia care provided by HCWs, with foreseeable client ability to remain independently living at home.

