### Other data collection and routine data

Client cognition and functional performance will be assessed by the trained research team using the Rowland Universal Dementia Assessment Scale (RUDAS) at enrolment and is not an outcome measure (35). Relevant medical and care related documentation will also be collected from home care service providers.

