### Visits

Assessment visits are scheduled in period 1, 2, and 3: baseline, 6 months, and 12 months respectively. All participants will be assessed as outlined in Fig. 2.

Prior to the COVID-19 pandemic, client and family carer assessments were conducted face-to-face at the participant’s home, although, if preferable, participants could choose to be assessed at the lead organisation or at a study partner University. HCW assessments were also conducted face-to-face either in their home, at the lead organisation, or at the home care provider’s offices, as preferred by the HCWs. Due to the COVID-19 pandemic, assessment visits are now conducted remotely, to protect the health and safety of participants and researchers. During the pandemic, client and family carer assessments are conducted via telephone, and HCW assessments are conducted only via online questionnaires using the lead organisation’s survey platform (REDCap).

Prior to COVID-19, client and family carer face-to-face assessments took approximately 1 h each to complete. Similarly, client and family carer telephone assessments during the pandemic took approximately 1 h each. The cognitive screening assessment was modified for suitable use over the telephone. These include involving the family carer in administering the visuo-spatial orientation and visuo-constructional drawing tasks and the removal of the praxis task. Family carer telephone assessments remained unchanged.

Prior to COVID-19, HCW assessments took approximately 30 min to complete. During the pandemic, HCWs were able to complete assessments online.

At the start of the pandemic, additional questions regarding the impact of COVID-19 were added to the assessments for HCWs, clients, and family carers.

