### Statistics and data analysis

Baseline variables will be fully described using descriptive statistics. The primary (sense of competency) and secondary (dementia knowledge, attitudes, work strain) outcomes for HCWs will be analysed using linear mixed models or generalised linear mixed models (depending on the data distribution and extent of unequal cluster sizes). Secondary outcomes for clients living with dementia and family carers (social care, client experience, health-related quality of life, neuropsychiatric symptoms, disability, carer role strain, dyadic relationship) will be compared pre versus post intervention periods using linear mixed models or generalised linear mixed models. Time and intervention will be represented in these models as fixed effects, whilst cluster and participants will be represented as random effects.

All-cause client transition from the home will analysed using survival analysis, employing Cox proportional hazards modelling and Kaplan-Meier survival curves. Clients of HCWs who did and did not receive PITCH training will be compared using Log rank tests. A prospective economic evaluation will be used to inform the cost-effectiveness of the PITCH program. Incremental costs will be estimated relative to the controls. Quality of life measures will be used to estimate a quality-adjusted life year (QALY) profile for participants. This will be used to estimate the cost per QALY. Statistical uncertainty and sensitivity analyses will be included with these results. Intention-to-treat methods will be used to account for missing data. For missing data, based on the pattern of missingness, we will use either multiple imputation techniques, selection, or pattern mixture models, in consultation with a statistician.

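### The comparison of time to transition from home is fixed as a log-rank test, which uses neither the baseline severity already collected nor the randomised regions; a prespecified adjusted Cox model would be a cheap gain in precision

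*Protocol article*

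**What the plan says.** All-cause transition from home is listed under Other outcomes and is also one of the hypotheses in the Background. Two consecutive sentences in Statistics and data analysis cover its analysis: "All-cause client transition from the home will analysed using survival analysis, employing Cox proportional hazards modelling and Kaplan-Meier survival curves", and then "Clients of HCWs who did and did not receive PITCH training will be compared using Log rank tests". Neither gives a covariate, a stratification factor or a term for cluster. Random effects for cluster and fixed effects for time are stated just before, for the mixed models only.

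The severity data are collected. Under Other data collection and routine data, the article states: "Client cognition and functional performance will be assessed by the trained research team using the Rowland Universal Dementia Assessment Scale (RUDAS) at enrolment". Under Secondary outcomes: "Functional daily activities of people with dementia in community dwelling will be assessed using the Disability Assessment for Dementia Scale (DAD". Under Outcome measures: "Measures are obtained at three time-points (periods 1, 2, and 3: baseline, 6 months, and 12 months respectively", so DAD has a baseline value. The only use stated for baseline variables as such is description. RUDAS changed when assessments moved to the telephone: the Visits section reports that family carers helped to administer two tasks, and also "the removal of the praxis task".

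Eligibility is wide: "Adult with a diagnosis of dementia (of any type and stage". Regions are allocated in blocks, with no stratification by severity stated. The number of regions is 18 in the Abstract and 12 under Sample size, and the Fig. 1 legend speaks of groups of 8. About 108 clients are expected. Control regions are trained 6 months after baseline.

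**The concern.** The client outcomes listed for mixed models are measured repeatedly, so their own baseline enters the model. Time to transition has no such baseline value. Severity at enrolment is a plausible strong predictor of leaving home, it varies widely under these criteria, and few units are randomised. The one test attached to the comparison cannot use it. If the SAP adjusts the Cox model, the plan still has two analyses of one endpoint with no stated order.

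The same sentence has two further weaknesses that bear on the remedy. A plain log-rank test treats clients as independent although regions are allocated. And whether a client's workers have been trained is not a fixed grouping: every region is eventually offered training, and control regions cross over during follow-up. Training is also not compulsory (Intervention Procedures), so a grouping by receipt, read literally, departs from allocation.

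At stake are the precision and credibility of the result on remaining at home.

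**Working it through.** **The plan's own figures.** No event count, hazard ratio or power is given for this endpoint. The only powered figure concerns the primary outcome (12 × 15 = 180 HCWs; 180 × 1.2 = 216), and this point does not rest on it.

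**Inputs.** From the document: 108 clients; 18 or 12 regions, hence 6 or 9 clients per region. Assumed, because the document is silent: severity hazard ratio 1.5 to 2.0 per SD, severity ICC 0.05 (0.10 as a variant), and 20% to 35% of clients with an event, that is 108 × 0.20 ≈ 22 to 108 × 0.35 ≈ 38 events.

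**Step 1: size of a chance imbalance.** With k regions of m clients, the SD of the between-arm difference in mean severity is √[2 × (ICC + (1 − ICC)/m) / (k/2)].
- k = 18, m = 6, ICC 0.05: √[2 × (0.05 + 0.95/6)/9] = 0.215 SD.
- k = 12, m = 9, ICC 0.05: √[2 × (0.05 + 0.95/9)/6] = 0.228 SD.
- ICC 0.10: 0.236 (18 regions) and 0.258 (12 regions).

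**Step 2: effect on the apparent hazard ratio when training does nothing.** Approximately (hazard ratio per SD)^imbalance. For 18 regions and ICC 0.05:
- imbalance of one SD of the difference: 1.5^0.215 = 1.09 to 2.0^0.215 = 1.16;
- imbalance of 1.96 times that: 1.19 to 1.34.

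Across 12 or 18 regions and ICC 0.05 to 0.10, the ranges are 1.09 to 1.20 and 1.19 to 1.42. In the sixth of allocations where one arm is worse by more than one SD of the difference, the mean excess is about 1.525 × 0.215 = 0.33 SD, giving 1.14 to 1.26. The opposite sixth errs by the reciprocal, 0.80 to 0.88, so the errors cancel over allocations.

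**Step 3: power and error with and without adjustment.** Simulation of 700 trials per setting (18 regions, 20% events by 6 months, ICC 0.05, one severity covariate, no other region effect); power is for a true hazard ratio of 0.5:

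| Quantity | Unadjusted | Adjusted |
|---|---|---|
| Null rejection, all allocations | 4% to 6% | 4% to 6% |
| Power, all allocations | 22% to 24% | 24% to 29% |
| Mean null hazard ratio, unfavourable sixth | 1.19 to 1.21 | 0.98 to 1.05 |
| Power, unfavourable sixth | 12% to 17% | 28% |

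The SD of the log hazard ratio was about equal for both analyses (0.42 to 0.45 under the null). The last two rows rest on about 700/6 ≈ 117 trials, so their Monte Carlo errors are about 0.43/√117 ≈ 4% on the hazard ratio and √(0.28 × 0.72/117) ≈ 4 points on power. A further simulation with two noisy severity covariates, closer to RUDAS plus DAD, gave null rejection near 5% either way and an overall power gain of about 1 to 4 points. In unfavourable allocations its null hazard ratio was about 1.1 to 1.3 unadjusted and 1.0 to 1.1 adjusted.

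**Step 4: what adjustment does not cure.** Ignoring clusters multiplies the variance by DE = 1 + (m − 1) × ICC of the outcome, and the true error of a 5% test is 2 × [1 − Φ(1.96/√DE)].
- 18 regions: DE 1.05, 1.25 and 1.50 at ICC 0.01, 0.05 and 0.10, giving 5.6%, 8.0% and 11.0%.
- 12 regions: DE 1.08, 1.40 and 1.80, giving 5.9%, 9.8% and 14.4%.

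A simulation of 3,000 runs per setting (30% events) agrees. With severity as the only source of region differences, log-rank rejection under the null was 4.4% to 6.3% for severity ICC 0 to 0.10. With an added region frailty (SD 0.4, severity ICC 0.10, hazard ratio 2.0 per SD), severity adjustment moved the error only from 8.5% to 7.6% (18 regions) and from 10.9% to 10.5% (12 regions).

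**The case against.** The strongest reply is that Cox modelling is named in the sentence before the log-rank test. A condensed article leaves its covariates to the SAP, which is not shown, so adjustment is not ruled out. That is right, and the missing covariate list is no fault. What remains is that the article does fix the test for the comparison, and that test cannot adjust.

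A second reply is that chance imbalance under randomisation is sampling error, already covered by the test's error rate. This also stands. A reader might infer that severity differences between regions bias the result or pass as a training effect more often than 5% allows. The calculations do not support that: null rejection is about the same with and without adjustment, and the large conditional figures have a mirror image in the other direction. The reply does presume comparison by allocation, which the wording about receipt of training leaves open.

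Third, the overall gain is small, the inputs are assumed, and region effects unrelated to severity are untouched. All true, which is why adjustment alone is not a sufficient remedy.

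Nor can it be said that RUDAS goes unused: baseline variables are to be described. It has no stated use beyond that.

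**Conclusion.** The point holds as a modest precision and prespecification issue. Fixing the comparison as a log-rank test leaves collected prognostic information and the region structure unused. Under the stated assumptions (severity hazard ratio 1.5 to 2.0 per SD, ICC 0.05, 20% to 35% events), the cost is roughly 1 to 5 points of power overall and more in unfavourable allocations, where the apparent null hazard ratio is about 1.1 to 1.3 unadjusted against about 1.0 to 1.1 adjusted. Overall type I error is not inflated by severity imbalance as such. Any inflation comes from ignoring regions and depends on an outcome ICC that the document does not give. Power for a true hazard ratio of 0.5 stays below 30% over all allocations either way, so adjustment does not make this endpoint well powered. The endpoint is neither primary nor secondary, and the conclusion on sense of competence is untouched.

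**What to change.** State in Statistics and data analysis that the main comparison for transition from home is a Cox model with:
- training as a time-varying exposure that follows each region's allocated schedule, not individual receipt;
- baseline RUDAS and baseline DAD as prespecified covariates. For RUDAS, use only items administered equivalently face-to-face and by telephone, or add a term for mode. Dropping praxis alone is not enough, because family carers also helped with the visuo-spatial and drawing tasks by telephone;
- a region frailty or cluster-robust variance, the latter with a small-sample correction given 12 to 18 regions.

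Keep the Kaplan-Meier curves and the log-rank test as descriptive.

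The cost is a sentence or two of text and no new data. The downside is a few extra parameters on few events: with training, RUDAS, DAD and a mode term there are four coefficients, or 22/4 = 5.5 to 38/4 = 9.5 events each. The covariate list should therefore stop there.

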### Data handling

A case report form (CRF) for each participant will be created to collect study data. Data is stored in a re-identifiable format. Identifiable information is treated as confidential and securely stored separately. Record storage and retention follows the Good Clinical Practice Guidelines. Identifiable information is securely stored in password-protected files at the lead organisation and/or on REDCap located on the lead organisation’s servers. All data will be destroyed seven years after the last publication of the project.

### Data monitoring

As we do not anticipate study related harms due participating in the study, there will be no stopping guidelines to terminate the trial nor interim analysis planned.

## Discussion

This paper describes a pragmatic stepped-wedge cluster-randomised controlled trial (SW-CRT) to evaluate a dementia training programme (PITCH) for paid HCWs. The aim of PITCH is to increase the competency and knowledge of the aged care workforce, as well as improve outcomes for clients living with dementia and their family carers.

Also described are some modifications to the protocol in response to the COVID-19 pandemic. In Australia, new national and state guidelines and regulations were devised to safeguard people in the aged care sector from the pandemic. Aged care providers likewise developed their own organisational policies in response. Due to these regulations and policies, aged care service providers limited access to their HCW staff and clients if the purpose was for research activities. In response, the PITCH programme is being adapted to be deliverable through an online platform. Likewise, HCW assessments are conducted using online questionnaires. Client and family carer assessments are also conducted via telephone when necessary.

## Trial status

The study is currently ongoing at the time of submitting this manuscript (September 2021), using protocol version 8 (14 July 2020). Recruitment started on June 2019, and the study is expected to be completed in April 2022.

### Ancillary and post-trial care

There is no anticipated harm and compensation for trial participation by HCWs.

### Dissemination policy

The datasets analysed during the current study will be available from the corresponding author on reasonable request. The results of the trial will be prepared for publication, and other dissemination strategies such as web, print, and conference presentations will be employed. There are no publication restrictions for this trial.

## Data Availability

Resultant data sets may be made available upon reasonable request of the corresponding author once the study is concluded.

## Abbreviations

HCW: Home care workers
NHMRC: National Health Medical Research Council
PITCH: Promoting Independence Through quality dementia Care at Home
